## Abstract

**Background:**

Patients with colorectal cancer (CRC) receiving chemotherapy often experience psychoneurological symptoms (PNS; ie, fatigue, depression, anxiety, sleep disturbance, pain, and cognitive dysfunction) that negatively impact both patients’ and their caregivers’ health outcomes. Limited information is available on PNS management for CRC patient and caregiver dyads.

**Objective:**

The purposes of this study are to (1) develop a web-based dyadic intervention for patients with CRC receiving chemotherapy and their caregivers (CRCweb) and (2) evaluate the feasibility, acceptability, and preliminary effects of CRCweb among patient-caregiver dyads in a cancer clinic.

**Methods:**

A mixed methods approach will be used. Semistructured interviews among 8 dyads will be conducted to develop CRCweb. A single-group pre- and posttest clinical trial will be used to examine the feasibility, acceptability, and preliminary effects of the intervention (CRCweb) among 20 dyads. Study assessments will be conducted before (T1) and after intervention (T2). Content analysis will be performed for semistructured interviews. Descriptive statistics will be calculated separately for patients and caregivers, and pre-post paired *t* tests will be used to evaluate treatment effects.

**Results:**

This study was funded in November 2022. As of April 2023, we have obtained institutional review board approval and completed clinical trial registration and are currently recruiting patient-caregiver dyads in a cancer clinic. The study is expected to be completed in October 2024.

**Conclusions:**

Developing a web-based dyadic intervention holds great promise to reduce the PNS burden in patients with CRC receiving chemotherapy and their caregivers. The findings from this study will advance intervention development and implementation of symptom management and palliative care for patients with cancer and their caregivers.

**Trial Registration:**

ClinicalTrials.gov NCT05663203; https://clinicaltrials.gov/ct2/show/NCT05663203

**International Registered Report Identifier (IRRID):**

PRR1-10.2196/48499

## Introduction

Colorectal cancer (CRC) is the third most common cancer and the second leading cause of cancer-related deaths in the United States [1]. Patients with CRC receiving chemotherapy often experience severe and distressing psychoneurological symptoms (PNS) that include fatigue, depression, anxiety, sleep disturbance, pain, and cognitive dysfunction [2-5]. When these multiple co-occurring symptoms are undertreated, they negatively affect functional status, survival rates, and quality of life (QOL) of patients and decrease health outcomes (eg, QOL and mood) of their family caregivers (hereafter “caregivers,” defined as family members or significant others identified by the patients as their primary source of emotional and physical support) [6-8]. Current interventional studies in context of CRC are mainly focused on CRC screening and treatment regimens [9,10]. Limited information is available on symptom management for patients with CRC and their caregivers, which underscores the critical need to develop an innovative and effective intervention to manage PNS for patient and caregiver dyads.

Evidence has shown that PNS may share similar mechanisms, such as increases in proinflammatory responses or neurotransmitter alterations, which partially explains why they cluster together [11,12]. Our prior work shows that depression and fatigue are core symptoms within PNS networks and that PNS are highly interconnected with each other over time, suggesting that symptom management for these clustered symptoms may decrease multisymptom burden at the same time [13]. Moreover, addressing multiple symptoms simultaneously is cost-effective as shown in prior research [14,15]. Although interventions have been developed for managing single symptoms (eg, pain and fatigue) [16,17], little is known about multiple PNS management.

Among current interventional programs, psychosocial strategies that decrease stress and improve psychosocial adaptation for individuals have demonstrated the potential of alleviating PNS as a cluster [18-22]. One evidence-based psychosocial intervention, the FOCUS program (ie, Family involvement, Optimistic attitude, Coping effectiveness, Uncertainty reduction, Symptom management), has shown to improve multiple co-occurring symptoms including PNS for patients with heterogeneous cancer diagnoses (eg, breast cancer and advanced CRC) and their caregivers [23-25]. However, FOCUS has several notable limitations, including an in-person delivery format that is costly and time-consuming. It is also not specific to PNS management and does not target patients with CRC receiving chemotherapy.

In addition, patients with CRC are facing unequal access to palliative care and disparities in treatment [26]. Prior studies reported that patients with CRC on Medicare and living in rural areas were more likely to experience severe symptom burden and treatment disruptions compared with those on private insurance and living in urban areas [27,28]. A technology-based approach (eg, web program) using computers and mobile devices allows high flexibility and accessibility for disproportionately affected patients with CRC and caregivers, especially during and after COVID-19, and minimizes the cost of the intervention in hectic and costly cancer clinics [29,30]. Therefore, developing a web-based dyadic intervention holds great promise to reduce PNS burden for both patients and their caregivers as well as to advance intervention development and implementation in cancer palliative care and health equity.

To our knowledge, there is no current web-based dyadic intervention for PNS management among patients with CRC and their caregivers. Therefore, the aims of this study are to (1) develop a web-based dyadic intervention to manage PNS for patients with CRC receiving chemotherapy and their caregivers (CRCweb) and (2) evaluate the feasibility, acceptability, and preliminary effects of CRCweb among patient-caregiver dyads in a cancer clinic.

## Methods

### Conceptual Model

Leveraging the FOCUS program [23-25] and health education theory [31], we developed a web-based dyadic intervention model (Figure 1). The FOCUS program provides the rationale for psychosocial education (eg, coping strategies) [32] and family involvement and support by including family members in the care process and educating families to cope with multiple demands [33]. Health education theory provides the basis for enhancing the patient-caregiver communication process and working in team science [31]. We hypothesize that the CRCweb intervention will enhance PNS management by reducing symptom burden and increasing QOL through improving psychosocial education and family involvement and support for patients with CRC receiving chemotherapy and their caregivers.

**Figure 1 figure1:**
[figure not shown]
The web-based dyadic intervention model (CRCweb).

### Design

The proposed study will be conducted in 2 phases—CRCweb development in phase 1 and a pilot clinical trial in phase 2. A mixed methods approach will be used. In phase 1, we will determine tailored content through qualitative interviews with patient-caregiver dyads, develop a web-based program prototype, and test program usability and refine the program to yield a final version of CRCweb. In phase 2, we will conduct a single-arm, pre- and posttest clinical trial to evaluate the feasibility, acceptability, and preliminary effects of the intervention on PNS and QOL among patient-caregiver dyads in a cancer clinic.

### Participants and Settings

In phase 1, we will recruit 8 patient-caregiver dyads; in phase 2, we will recruit 20 dyads. The inclusion criteria for patients will be age ≥18 years, diagnosed with CRC (any cancer stage), life expectancy >12 months, receiving active chemotherapy, self-reported at least 2 PNS (based on the symptom measures’ cutoff scores described in Table 1), identified primary caregiver, access to the internet, and fluent in English. Patients who have a Karnofsky Performance Scale score of <50 will be excluded. The inclusion criteria for caregivers will be age ≥18 years, primary caregiver, self-reported at least 2 PNS (based on the symptom measures’ cutoff scores described in Table 1), access to the internet, and fluent in English. Caregivers who have severe diseases such as cancer and heart disease will be excluded. Patients will be recruited at the Gastrointestinal Oncology Clinics of Emory Winship Cancer Institute.

**Table 1 table1:** Measurements.

Outcome and variable				Time point^a^		Description

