**Secondary outcomes^b^**						
	**Intervention effect**					
		Psychoneurological symptoms	T1, T2		Fatigue: 20-item Multidimensional Fatigue Inventory. A cutoff score of ≥43.5 indicates moderate-to-severe fatigue. Depression: 8-item Patient Health Questionnaire. A cutoff score of ≥10 indicates clinically significant depression. Anxiety: Spielberger State Anxiety Inventories. A cutoff score of >32.2 indicates high levels of state anxiety. Sleep disturbance: Pittsburgh Sleep Quality Index (PSQI). PSQI score of ≥5 indicates a significant level of sleep disturbance. Cognitive dysfunction: Attentional Function Index (AFI). AFI score of <5 indicates a significant level of cognitive dysfunction. Pain: Brief Pain Inventory. A cutoff score of ≥4 indicates moderate to severe pain.	
		Quality of life	T1, T2		The Short Form-12 consists of 12 questions about physical and mental health as well as overall health status. It is scored into 2 components: physical component score (PCS) and mental component score (MCS). Higher PCS and MCS scores indicate a better quality of life.	

^a^T1: before intervention, at baseline; T2: after intervention.

^b^The details for the measures can be found in Multimedia Appendix 1.

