### Ethics Approval

The study was approved by the institutional review board at Emory University (STUDY00004750) and registered at the CliniclTrials.gov (NCT05663203). Participants will be recruited from May 2023 to August 2024 at the Emory Winship Cancer Institute. The research staff will screen eligible patients in the electronic health record system (Epic); they will then reach out to health care providers at the clinic who will confirm eligibility and suitability and give permission for the research staff to reach out to the patient-caregiver dyads to assess their interests. If the research staff find that both patients and caregivers are interested, they will explain the study to dyads and obtain dyads’ written informed consent in person at the clinic.

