### Phase 2—Pilot Clinical Trial

We will conduct a single-arm, nonrandomized, and nonblinded pre- and posttest clinical trial among patients with CRC receiving chemotherapy and their caregivers (n=20 dyads). Primary outcomes (feasibility and acceptability) will be assessed at the completion of intervention among patients and caregivers. Secondary outcomes (PNS and QOL) will be assessed at baseline (T1, before intervention) and 8 weeks (T2, after intervention) for patients and caregivers. We will collect quantitative assessment data on internet-accessible devices via REDCap self-administered surveys. We will avoid collecting symptom data at the acute symptoms stage (within 1 week after chemotherapy administration) to reduce measurement bias. Additionally, semistructured formative evaluation interviews will be conducted after the intervention among these participants regarding their experiences and suggestions on the intervention to inform the future refinement.

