In phase 2, quantitative data will be analyzed using SPSS Statistics (version 27.0; IBM Corp). Descriptive analyses will be conducted to determine the frequencies, percentages, means, and SDs of major variables. Feasibility of study attrition and adherence will be assessed by calculating attrition rates, identifying reasons for refusal, and assessing completeness of the data. Accessibility of participant satisfaction will be evaluated by calculating descriptive statistics to summarize responses to the poststudy evaluation items. Pre-post paired *t* tests (and nonparametric equivalents as needed) will be used to evaluate the changes between secondary outcomes (PNS, using the same calculating methods as described in our previous publication [13]) from pre- to postintervention stages for patients and caregivers. We will use dyadic analyses because of the increasing evidence that patients’ and their family caregivers’ responses to illness are interrelated [14]. Time and level (ie, patient vs caregiver) will be treated as within-subject variables to control for the interdependent nature of the data. The main effect by time will be examined to determine the overall effect of intervention on PNS for patient-caregiver dyads as a unit (average scores across dyads) [40]. We will also analyze time-by-level interactions to determine if there will be a differential effect of the intervention on patients’ and caregivers’ outcomes [14]. As needed (for an adjusted analysis), potential covariates (eg, age, insurance, and income) will be included in the planned models as appropriate. Additionally, qualitative data from postintervention interview will use the same analysis as in phase 1. Convergent parallel analysis will be used to compare and merge the quantitative and qualitative data when they have been completed [41]. We will discuss areas of convergence or divergence between the quantitative and qualitative results to refine the intervention.

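### Entry requires high scores on the same symptom scales used as outcomes, and the single-arm pre-post change is then read as an intervention effect, with no statement that T1 is separate from screening

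*Protocol article*

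**What the plan says.** Under Participants and Settings, patients qualify only with "self-reported at least 2 PNS (based on the symptom measures’ cutoff scores described in Table 1". The same condition applies to the other dyad member: "The inclusion criteria for caregivers will be age ≥18 years, primary caregiver, self-reported at least 2 PNS".

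Table 1 gives the cutoffs, for example "A cutoff score of ≥43.5 indicates moderate-to-severe fatigue" and "A cutoff score of ≥10 indicates clinically significant depression". It lists the same six instruments as secondary outcomes at T1 and T2.

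The section Phase 2—Pilot Clinical Trial describes a single-arm, nonblinded study of 20 dyads. On timing it says: "Secondary outcomes (PNS and QOL) will be assessed at baseline (T1, before intervention) and 8 weeks (T2, after intervention".

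Two places attribute the change to the intervention. The Abstract (Methods) says of the paired comparisons that "tests will be used to evaluate treatment effects". Data Analysis says: "The main effect by time will be examined to determine the overall effect of intervention on PNS for patient-caregiver dyads as a unit".

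The Discussion names two pitfalls: selection through language and internet access, and attrition. It names neither selection on symptom scores nor the lack of a comparator.

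**The concern.** A person who qualifies by scoring high on a fluctuating scale tends to score lower when measured again, even if nothing has been done. If the qualifying score is also the baseline, that fall is counted as improvement. Both dyad members are selected this way, so it affects the patient tests, the caregiver tests and the dyad-level time effect. No control arm is available to subtract it.

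What is at stake is the preliminary-effects part of the second aim. A paired test against zero asks whether scores changed. It does not ask whether CRCweb changed them, and its nominal error rate does not apply to the second question.

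**Working it through.** **Is T1 the screening reading?** T1 is the only symptom assessment before the intervention that the article describes. Ethics Approval describes record screening, followed by contact with "health care providers at the clinic who will confirm eligibility and suitability". Neither step yields a caregiver's questionnaire scores. On the other side, Participants and Settings gives one set of criteria for both phases, and phase 1 dyads have no T1. The text leaves the question open, so the calculation below is conditional on screening scores serving as T1.

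**Inputs from the article.** Six symptoms; entry on at least 2 of 6 beyond cutoff; n=20; change T2−T1 tested against zero. The article gives no alpha, prevalence or retest figure.

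**Assumptions.** Normal scores in SD units, with higher meaning worse. Observed correlation between symptoms ρ=0.5. Fraction *q* of the screened population beyond each cutoff, 20-70%. Eight-week retest correlation *r*, 0.6-0.8. No true change. Two-sided alpha 0.05, counting significant improvements only (nominal 2.5%). Short-term fluctuations are either correlated 0.5 across symptoms or independent.

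**Formula.** Let *m* be the mean standardised score of those admitted.

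- Correlated fluctuations: expected fall = (1−r)·m
- Independent fluctuations: expected fall = (1−r)·m/(1+5ρ) = (1−r)·m/3.5

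Simulation gives *m* of about 0.83, 0.63, 0.35 and 0.15 for *q* of 20%, 30%, 50% and 70%.

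| q | r | Fluctuations | Fall (SD) | False improvement per symptom (simulated) |
|---|---|---|---|---|
| 20% | 0.6 | correlated | 0.4×0.83 = 0.33 | 37% |
| 30% | 0.7 | correlated | 0.3×0.63 = 0.19 | 18% |
| 50% | 0.8 | correlated | 0.2×0.35 = 0.07 | 7% |
| 70% | 0.7 | correlated | 0.3×0.15 = 0.05 | 4% |
| 30% | 0.7 | independent | 0.3×0.63/3.5 = 0.05 | 5% |
| 70% | 0.7 | independent | 0.3×0.15/3.5 = 0.01 | 3% |

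**Plausibility check on the central correlated case** (q=30%, r=0.7). The SD of a change score is about √(2(1−0.7)) = 0.77, so the standardised change is 0.19/0.77 = 0.25. With n=20 the test statistic is centred near 0.25×√20 = 1.1, not 0, which fits the 18%.

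**Any of six symptoms.** At q=30% and r=0.7, at least one false significant improvement occurs in 52% of trials with correlated fluctuations and 25% with independent ones. Multiplicity alone accounts for about 11% and 14% respectively, so only the excess is regression to the mean.

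**Dyad average.** Averaging over symptoms and dyad members reduces noise but leaves the shift in place. In the central correlated case, with dyad members taken as independent, a six-symptom composite shows false improvement in about 30% of trials and its dyad average in about 50%.

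**Separate T1.** If T1 is a new reading after screening and fluctuations do not persist between the two, the expected fall is 0.00 SD and the per-symptom rate returns to about 2.5%.

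**The case against.** A reader might infer that T1 certainly is the screening score and that the bias is therefore built in. The article does not say so. Phase 1 must use some symptom screen that is not T1. Phase 2 symptom data are also kept away from the week after chemotherapy, so T1 could fall on a different day from recruitment. The flow figure is not shown, and a condensed article may leave screening mechanics to the full protocol. This objection stands, and it is why the size is stated conditionally.

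The size also depends on unstated quantities. Correlated fluctuation multiplies the shift by 3.5 compared with independent fluctuation. It is plausible for symptoms that the Introduction describes as clustered and interconnected over time, but it remains an assumption. If most of the clinic population passes the cutoffs, the artefact is close to nil.

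A reader might also infer that the plan claims efficacy from a p value, or that this estimate will size a larger trial. Neither is in the text. No alpha or go/no-go rule is attached to the paired tests, and the Discussion says only that larger studies may follow.

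Nor can one infer that the net bias favours CRCweb. Patients remain on chemotherapy, and worsening over eight weeks could mask the drift as easily as improvement could add to it.

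None of this answers the attribution problem. Even with a separate T1, a single-arm change does not show the effect of the intervention.

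**Conclusion.** The point holds in two parts. The first is unconditional: the same scales select and measure participants, there is no comparator, and two passages nevertheless attribute the change to CRCweb. The second is conditional on screening scores serving as T1: regression to the mean alone then pushes every symptom towards apparent benefit. Under the stated assumptions the push runs from negligible to about a third of an SD. The central case (30% beyond each cutoff, retest 0.7) is 0.05 SD and 5% false improvement per symptom with independent fluctuations, or 0.19 SD and 18% with correlated ones. The article gives no figures that would narrow this range.

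Severity is moderate. Symptoms are a secondary outcome and their effects are labelled preliminary. Attrition, adherence and satisfaction, the primary outcomes, are untouched.

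**What to change.** 1. State under Phase 2—Pilot Clinical Trial that T1 is a fresh administration of the six instruments, after eligibility is confirmed and before CRCweb access, and that only this reading is the baseline. If this is already the practice, one sentence is enough. Otherwise the cost is one extra web questionnaire per participant and probably a smaller apparent change. Some regression to the mean may remain if fluctuations persist from screening to T1, so items 2 and 3 are needed in either case.
2. In the Abstract (Methods) and Data Analysis, replace the treatment-effect and intervention-effect wording with *uncontrolled pre-post change*. Report mean change with a 95% CI and do not attribute it to CRCweb. The cost is wording only.
3. Add regression to the mean and the absent comparator to the pitfalls in the Discussion. The cost is one or two sentences.

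A reliability-based correction instrument by instrument is not a sound substitute for item 1. The article gives no retest figures, and selection acts on a count of at least 2 of 6 symptoms, not on each scale separately.

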**Primary outcomes**						
	**Feasibility**					
		Attrition	T2		Attrition is measured by the number of patients and caregivers who drop out before completing the intervention. We will consider the intervention to have low attrition if >80% dyads remain enrolled.	
		Adherence	T2		Adherence is measured by the number of modules completed for dyads. It is determined by high adherence if dyads complete >80% of the modules.	
	**Acceptability**					
		Satisfaction	T2		Participant satisfaction with CRCweb is assessed by the 8-item Client Satisfaction Questionnaire (Cronbach α=.93; 8-item; 4-point Likert) among patients and caregivers at the end of the intervention.	
**Secondary outcomes^b^**						
	**Intervention effect**					
		Psychoneurological symptoms	T1, T2		Fatigue: 20-item Multidimensional Fatigue Inventory. A cutoff score of ≥43.5 indicates moderate-to-severe fatigue. Depression: 8-item Patient Health Questionnaire. A cutoff score of ≥10 indicates clinically significant depression. Anxiety: Spielberger State Anxiety Inventories. A cutoff score of >32.2 indicates high levels of state anxiety. Sleep disturbance: Pittsburgh Sleep Quality Index (PSQI). PSQI score of ≥5 indicates a significant level of sleep disturbance. Cognitive dysfunction: Attentional Function Index (AFI). AFI score of <5 indicates a significant level of cognitive dysfunction. Pain: Brief Pain Inventory. A cutoff score of ≥4 indicates moderate to severe pain.	
		Quality of life	T1, T2		The Short Form-12 consists of 12 questions about physical and mental health as well as overall health status. It is scored into 2 components: physical component score (PCS) and mental component score (MCS). Higher PCS and MCS scores indicate a better quality of life.	

^a^T1: before intervention, at baseline; T2: after intervention.

^b^The details for the measures can be found in Multimedia Appendix 1.

